## Abstract

**Background:** Panic of the disease and the associated concerns can lower the quality of life and physical performance. As long as the COVID-19 pandemic is ever on the rise, the psychological pandemic of the disease is on the rise, too. The high prevalence of COVID-19 has further increased physicians' work pressure. Patients' needs are not met adequately by physicians. It seems essential to use aids to monitor patients' needs and serve them properly. Thus, in the present research, suggestions are made on how to evaluate patients' physical and psychological conditions during the treatment via a mobile application.

**Methods and Analysis:** The present research is a randomized, two parallel-group, controlled trial. One-hundred-twelve inpatients diagnosed with the coronavirus will be assigned randomly to the control and intervention groups. In the intervention group, a mobile application will be provided to educate patients, establish two-way interactions between patients and care providers and record patients' symptoms. Those in the control group will receive the usual care. The primary outcome is the change to the depression anxiety stress scales-21 (DASS-21) score from the baseline to 2 weeks after discharge from hospital. It will be measured at the baseline, at the time of discharge, and two weeks later.

**Ethics and Dissemination:** The Ethics committee of Mashhad University of Medical Sciences' approval date was 2020-04-19 with IR.MUMS.REC.1399.118 reference code. Thus far, participants' recruitment has not been completed and is scheduled to end in March 2021. The results will be disseminated in a peer-reviewed journal.

**Trial Registration:** IRCT20170922036314N4 (https://www.irct.ir/trial/47383).

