### Sample Size

The similar research was used to estimate the sample size. The most similar study to the present work was conducted by Proudfoot et al. (31), who explored the effect of a mobile application on stress, anxiety and depression. In the above-mentioned research, after the intervention, the effect size between the control and intervention group (the one provided with the application) was reported to be 0.41. The sample size is estimated 190 in total (95 for the intervention group and 95 for the control group) which is calculated in G^*^Power software with an effect size of 0.41, error probability of 0.05, power of 0.8, and allocation ratio of 1:1. Regarding the 10 % attrition rate within the study, the goal is to include 105 patients in each group (210 participants overall).

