### Statistical Analysis

The normal quantitative variables (checked via the Kolmogorov–Smirnov normality test) will be described using mean and standard deviation. The rest of data will be described using median and interquartile range. To compare the two research groups in terms of the mean difference of quantitative variables, if the normality assumption is met, an independent-sample *T*-test will be run. Otherwise, Mann–Whitney *U*-test will be employed. To test the homogeneity of qualitative variables in the two groups, the Chi-squared test and Fisher's exact test will be run at the *p*-value of 0.05. Repeated-measures or equivalent non-parametric tests will be employed for the continuous outcomes measured repeatedly. All these tests will be two-tailed at a 5 % significance level. Statistical analyses will be done in SPSS22. The analysis will be conducted on an intention to treat. No interim analyses are planned.

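### The abstract randomises 112 patients but the Sample Size section sets 210; at 112 the stated 80% power falls to about 53–58%

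*Protocol article*

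**What the plan says.** The Abstract, under Methods and Analysis, gives the number to be randomised: "One-hundred-twelve inpatients diagnosed with the coronavirus will be assigned randomly to the control and intervention groups".

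The Sample Size section gives a different number and derives it. It takes a standardised effect from a similar study of a mobile application: "the effect size between the control and intervention group (the one provided with the application) was reported to be 0.41". The other inputs are "error probability of 0.05, power of 0.8, and allocation ratio of 1:1". The result is "The sample size is estimated 190 in total (95 for the intervention group and 95 for the control group"). An allowance follows for "Regarding the 10 % attrition rate within the study", and then the enrolment target: "the goal is to include 105 patients in each group (210 participants overall").

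The Statistical Analysis section fixes the test that these numbers serve. Groups are compared by t-test ("if the normality assumption is met, an independent-sample" version), or by Mann–Whitney otherwise. On sidedness it says "All these tests will be two-tailed at a 5 % significance level". It also says that no interim analysis is planned. The Abstract and the Results section both say that recruitment has not finished and is due to end by March 2021.

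**The concern.** Both totals are forward-looking statements of how many patients the trial will enrol, and they differ by 210 − 112 = 98 patients; 112 is 53% of 210. The smaller number matches nothing in the Sample Size section: not the evaluable total (190), the enrolled total (210), or either per-group figure (95 or 105). The article nowhere describes 112 as a per-group number, a count to date or a revised target.

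If 112 is the working target, the 80% power claim is false for the trial's own effect size, and a true effect of 0.41 would be missed more than four times in ten. If 210 is the working target, the most widely read part of the article understates the trial's size by almost half. Because recruitment is open, the number that ends enrolment is still a live question. With two totals in print, a trial that stopped at either could be described as having run to plan.

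**Working it through.** **Inputs.** Standardised effect d = 0.41, α = 0.05, power 0.80, 1:1 allocation and 10% attrition, all from Sample Size. Two-sided testing and the two-sample t-test come from Statistical Analysis. The total of 112 comes from the Abstract.

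**Method.** For n per group, the t statistic has 2n − 2 degrees of freedom and noncentrality d·√(n/2). Power is the probability that it exceeds the two-sided 5% critical value in absolute terms.

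**Step 1: reproduce the plan's figure.**
- Normal approximation: n = 2(1.960 + 0.842)² / 0.41² = 93.4, so 94 per group (188 in total).
- Noncentral t, as G*Power uses for a t-test: n = 94.35, so 95 per group and 190 in total. This matches the article exactly.
- A one-sided test would need only 75 per group (74.24 rounded up), so the article's figure is two-sided, as Statistical Analysis says.

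**Step 2: reproduce the attrition allowance.**
- 95 × 1.10 = 104.5, rounded to 105 per group, or 210.
- Dividing by the retained fraction gives 95 / 0.90 = 105.6, so 106 per group, or 212. The difference is immaterial: 105 × 0.90 = 94.5 evaluable per group still gives 80.1% power.

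**Step 3: power at the abstract's total.** 112 / 2 = 56 per group; 56 × 0.90 = 50.4, so about 50 after attrition.

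| Evaluable per group | Source | Noncentrality | Power (noncentral t) | Power (normal) |
|---|---|---|---|---|
| 95 | Sample Size, evaluable | 0.41 × √47.5 = 2.83 | 80.3% | 80.7% |
| 94.5 | 210 enrolled, 10% lost | 0.41 × √47.25 = 2.82 | 80.1% | 80.5% |
| 56 | 112 enrolled, none lost | 0.41 × √28 = 2.17 | 57.6% | 58.3% |
| 50 | 112 enrolled, 10% lost | 0.41 × √25 = 2.05 | 52.8% | 53.6% |

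**Step 4: effect detectable with 80% power.** Solving the same equation for d gives 0.534 at 56 per group and 0.566 at 50 per group.

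**Step 5: could another reading rescue 112?**
- One-sided 5%: power is 65.2% at 50 per group and 69.5% at 56. It is still short of 80%, and the two-tailed statement excludes it.
- 112 per group: the total would be 224, which contradicts 105 per group.

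**The case against.** The strongest reply is that this may be no more than a stale or mistyped number in a summary. The Sample Size section is the dedicated, worked statement and it reproduces; the Abstract offers a bare figure with no derivation. If 210 is what the team is recruiting, the design has no power problem. That is fair, and it is why the power loss must be read as conditional on 112. It does not remove the contradiction, and the article alone cannot show that 112 is a slip: the number is written out in words and divides evenly into two groups of 56, as a real 1:1 target would.

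Second, 53–58% is the power of a simple two-sample t-test. The primary outcome is change from baseline and repeated-measures tests are also planned. If 0.41 is an effect on the post-intervention score, power for change depends on the correlation r between baseline and follow-up, which the article does not give for these patients. Assuming equal variances, the effect on change is 0.41/√(2(1 − r)). With 50 to 56 per group, power is then about 40–44% at r = 0.3, 53–58% at r = 0.5 and 75–79% at r = 0.7. So 53–58% should be labelled as the figure under the plan's own method. This does not rescue 112: the plan assumes no correlation and rests its 80% on the simple method, and even r = 0.7 leaves power below 80%.

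Third, one should not overstate the consequences. With 50 to 56 per group the 95% confidence interval has a half-width of about 0.37 to 0.40 standard deviations, so a null result would still carry some information. Nor does the article suggest that anyone is choosing between two stopping points: there is no interim analysis, the data analyst is to be blinded, and recruitment is tied to a date. Patients and the outcome assessor are not blinded, so the risk is not zero, but it is an inference. These points limit the rhetoric and leave the finding intact.

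**Conclusion.** The concern holds. The Abstract and the Sample Size section give incompatible enrolment totals in current text, and only 210 agrees with the stated 80% power. If 112 is the number recruited, power for an effect of 0.41 is 57.6% with no losses and 52.8% with 50 per group after 10% attrition, and the effect detectable with 80% power is 0.53 to 0.57. These figures assume a two-sided 5% two-sample t-test, equal groups, and 0.41 as the standardised effect on the outcome analysed, which is the basis on which the plan's own 190 reproduces. The article does not show which total is operative, so the power loss is conditional; the contradiction is not. Enrolment and power are core design facts that the article itself states, so this should be corrected.

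**What to change.** The team should confirm which total is being recruited and state that one number everywhere, as the only recruitment target.

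- **If it is 210:** correct the Abstract to 210 (105 per group). The Sample Size section stands. The cost is one number.
- **If it is 112:** rewrite the Sample Size section. Report that power for an effect of 0.41 is about 53% after 10% attrition and that the effect detectable with 80% power is about 0.57, and give the reason for the smaller target. The cost is a less favourable power statement.

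Neither route needs new procedures or data.

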## Introduction

Panic of the unknown can reduce perceived security in humans, and it has always been stressful. The prevalence of COVID-19 can be stressful too. The symptoms of the disease can range from mild to severe. The symptoms include fever, coughs, and shortness of breath (1). Anxiety is a common symptom in patients afflicted with a chronic respiratory disease and can lower the quality of life to a great extent. Clinical anxiety plagues about two-third of respiratory patients and also reduces the quality of life and physical performance. Anxiety induced by Covid-19 prevails and it seems to originate from the unknown nature of the disease and the ambiguity involved. Panic of the disease and the associated concerns might be so intense that it can provoke patients, adults and children. Often, people at a higher risk of the disease (those with diabetes, a transplant, hypertension, respiratory problems, etc.) react more severely to the disease (2).

Because COVID-19 pandemic is ever increasing, the psychological pandemic of the disease is also on the rise. New psychological problems have emerged due to the unreliability and instability of the coronavirus, bad news on the rapid transmission of the disease among people (3, 4), the unknown origin of the virus (5, 6), its high reproductivity (6) and the unpredictability of conditions. Besides the physical suffering, the increased mental pressure involved in confirmed cases of the disease or suspicious circumstances can exacerbate the condition (7, 8). Anxiety and panic can worsen the shortness of breath and reduce patients' adherence to physicians' advice and can even worry the medical staff. If so, patients may experience loneliness, denial, anxiety, depression, sleeplessness, and disappointment. This can reduce the rate of adherence to medical treatment. Some cases may even increase the chances of aggression and suicide (9). Besides inpatients, those discharged also experience different degrees of stress even after the end of the event.

On the other hand, at present, the high prevalence of COVID-19 has further increased physicians' work pressure. Patients' needs are not met adequately by physicians. It seems essential to use aids to monitor patients' conditions and serve them properly. As previously mentioned, COVID-19 patients are affected both physically and psychologically. They need support from both sides.

The current pandemic makes it essential to explore the different aspects of psychiatry, including social-psychological and medical interventions, to find effective evidence-based treatments. One way to reduce patients' stress is to run medical programs and report the health state to them, which can be provided in multiple ways (10).

The past decades have witnessed advanced digital technologies and, thus, the relevant revolutions are pretty promising. New technologies can cost-effectively improve health service provision. Today, many people can access such technologies at a low cost, especially technologies based on smartphones and mobile applications, which have attracted the global population. Thus, it seems that mobile-based interventions play a key role in providing medical services during the pandemic.

Mobile health solutions can potentially provide valuable services during the COVID-19 pandemic. These services can be in the form of education, resource allocation, surveillance, screening, treatment, diagnosis, prevention, management, and control (11).

Applications for contact tracing, symptom monitoring and information provision are among the critical applications developed to manage COVID-19 pandemic (12). Though many applications have been developed for COVID-19, many do not have the right quality (11).

A significant body of research has dealt with the effectiveness of self-care applications and software from physical and psychological aspects in different patients (13–16).

A body of research explored the role of mobile applications in mental health (17, 18). The findings of these studies along with the results of a review in 2019 (19) show that applications play a key role in reducing the symptoms of depression. Besides the patients, physicians' attitude toward the use of mobile-based interventions is positive and promising. Physicians' and patients' acceptance of mobile applications in this field contributes to the use of mobile-based devices for self-management in mental diseases. Due to the notable limitations of the pandemic (e.g., the quarantine, less social contact, and consequently less face-to-face referral to care-providing centers), attention has been drawn to telehealth approaches to facilitate the mental health-related services (20–23). Due to the effectiveness of mobile-based interventions in mental health domain, during the pandemic, mobile-based interventions can be used as non-drug interventions with almost no adverse effect on the COVID-19 patients. These can help reduce depression and anxiety (24).

Thus, in the present research the aim is to evaluate patients' physical and psychological conditions during the treatment (both during hospitalization and recovery) via a mobile application. To this aim, the data stored in the application which represent the patients' condition during the disease will be analyzed by a team of experts consisting of physicians and psychologists. It is expected that removing patients' ambiguities by teaching medical and psychological content, monitoring patients during hospitalization and recovery, and sending them feedback by the physician help reduce mental pressures and improve the medical treatment.

## Methods

### Study Design and Setting

A randomized, two parallel-group, controlled trial is designed following the Consolidated Standards of Reporting Trials guidelines (25) (Figure 1) to investigate whether the mobile application designed will make any difference in the emotional states of depression, anxiety, and stress in target patients and whether it will produce any better outcome in COVID-19 patients.

**Figure 1 F1:**
[figure not shown]
Schematic of the study procedure.

The study will be conducted in Imam Reza Hospital in Mashhad, Khorasan Razavi Province, Northeastern Iran. The center is affiliated with Mashhad University of Medical Sciences (MUMS). This hospital has been a referral center for COVID-19 patients since the start of the pandemic in Iran.

### Participants

The target population consists of patients hospitalized with the coronavirus. The eligible patients, based on the inclusion criteria, will be informed about the purpose of study. Then an assistant researcher will collaborate to obtain the written informed consent. It will be ensured that participants can withdraw from the study any time they wish with no effect on their subsequent care. The informed consent has already been evaluated by the Ethics Committee of MUMS (Ethical code: IR.MUMS.REC.1399.118).

#### Inclusion Criteria

baseline literacyusing a smartphoneability to work with a smartphone.

#### Exclusion Criteria

unwillingness to continue with researchtransference to the wards where it is not possible to use a mobile phone, such as the intensive care unitdeterioration of the patient's physical condition.

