### Outcome Measures

#### Primary Outcomes

The primary outcome will be a change to the patient's depression anxiety stress scales-21 (DASS-21) score from baseline to 2 weeks after discharge from hospital. It will be measured at the baseline, upon discharge and 2 weeks afterward. It should be noted that baseline measurements will be collected as soon as the patient is admitted to the hospital. This will ensure that almost all patients are included under the same conditions.

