#### Secondary Outcomes

Changes to the respiratory symptoms including the respiratory rate will be determined through physician assessment; oxygen saturation will be measured through pulse oximetry; lung involvement will be checked by imaging at the time of discharge.Changes to the non-respiratory symptoms including multi-organ failure will be determined through kidney and liver function tests; fever will be measured with a thermometer; secondary infection will be measured by physician assessment at the time of discharge.

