### Randomization

www.randomization.com will be used to create a randomization sequence. The sequence of the generated random number will be inserted into envelopes sealed by an independent researcher (SA), not participating in the main data collection phase or in the intervention. These envelopes will be opened only after the participants sign the informed consent and complete all baseline assessments (FK). Then, the eligible participants will be randomly divided into two groups, a usual care group and an intervention group, which uses the application.

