## Strengths and Limitations of this Study

The self-care mobile application in the present research was designed in a structured way with the help of a multi-disciplinary team.The application addresses specific, well-defined characteristics, including care-providers' education, contact, self-reported symptoms and care-providers' biography. These all can increase the chances of success.The design of this study (randomized controlled trial) tends to meet the highest level of evidence.We cannot blind patients to the nature of the intervention, and this is an alleged limitation in the present research.Some limitations of the present research are the low literacy of using mobile health in the target population and some patients' unwillingness to continue using the application.

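### The exclusion criteria are events that fall mainly after randomisation; excluding randomised patients for them conflicts, as written, with the stated intention-to-treat analysis

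*Protocol article*

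**What the plan says.** All references are to the protocol article.

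- **Exclusion Criteria.** There are three items and no others: being unwilling to go on with the research, being transferred "to the wards where it is not possible to use a mobile phone, such as the intensive care" unit, and physical deterioration. No time point or threshold is attached to any of them.
- **Participants.** The approach for consent rests on the inclusion list: "The eligible patients, based on the inclusion criteria, will be informed about the purpose of study".
- **Primary Outcomes.** On timing, "baseline measurements will be collected as soon as the patient is admitted to the hospital". On follow-up of DASS-21, "It will be measured at the baseline, upon discharge and 2 weeks afterward".
- **Randomization.** "These envelopes will be opened only after the participants sign the informed consent and complete all baseline assessments".
- **Statistical Analysis.** "The analysis will be conducted on an intention to treat".
- **Secondary Outcomes.** These include respiratory rate, oxygen saturation, lung involvement, secondary infection and organ failure: "Changes to the non-respiratory symptoms including multi-organ failure will be determined through kidney and liver function tests".
- **Blinding.** Patients and the outcome assessor are not blinded; the data analyst is.
- **Strengths and Limitations.** The authors expect some patients' "unwillingness to continue using the application".
- **Sample Size.** 95 per group for an effect size of 0.41, raised to 105 per group (210 in total) for 10% attrition. What counts as attrition is not stated.

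**The concern.** An exclusion criterion normally describes a state that can be checked before allocation. These three describe changes during participation. If a randomised patient who is moved to intensive care or deteriorates is excluded from the trial, the groups compared at the end are defined partly by what happened after allocation. An intention-to-treat analysis exists to prevent that.

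Two things are at stake. First, the DASS-21 comparison loses the protection of randomisation if removal differs between arms, either in how many patients go or in which kind. Second, whatever happens by arm, the patients taken out are those most likely to show low oxygen saturation, organ failure or secondary infection. The secondary outcomes would then describe a group selected for having done well.

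**Working it through.** **Step 1: order of events.** Baseline is at admission, then the envelope is opened, then follow-up runs through the stay to two weeks after discharge. Little time lies between admission and allocation. A patient cannot decline to continue before starting, and transfer or worsening during the stay will mostly come after the envelope is opened. The Participants section ties the approach for consent to the inclusion criteria alone, so the exclusion list is not presented there as a screening step. No section limits the three items to the period before randomisation, and none says that an excluded patient is still followed and analysed.

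**Step 2: reproduce the planned size.** Inputs from Sample Size and Statistical Analysis: d = 0.41, two-sided alpha 0.05, power 0.80, 1:1 allocation.
- Normal approximation: n = 2(1.960 + 0.842)² / 0.41² = 93.4, so 94 per group.
- t-based solution: 94.35, so 95 per group, as stated.
- Attrition: 95 × 1.10 = 104.5, so 105 as stated. Dividing instead, 95 / 0.90 = 105.6, would give 106; the difference is immaterial here.

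The figures below use 105 per group. (The Abstract gives 112 patients in total; that discrepancy is a separate matter.)

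**Step 3: power if randomised patients are removed equally from both arms** (two-sided t-test, d = 0.41):

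| Removed | Left per group | Power |
|---|---|---|
| 0% | 105 | 0.841 |
| 10% | 94 | 0.799 |
| 20% | 84 | 0.752 |
| 30% | 73 | 0.692 |

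**Step 4: bias and type I error with no true effect.** The assumptions are mine and are not in the article: the DASS-21 change score has SD 1; removed patients are D SD worse on that change score than retained patients, equally in both arms; the proportion removed is p_C in control and p_A in the app arm. With both arms averaging 0 before removal, the retained mean in an arm is −pD. Hence

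- bias = −(p_A − p_C) × D (negative favours the app)
- SE = √[1/(105(1 − p_C)) + 1/(105(1 − p_A))]
- type I error = Φ(−1.96 − bias/SE) + Φ(−1.96 + bias/SE)

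Example with p_C = 0.10, p_A = 0.20, D = 0.5: bias = −0.10 × 0.5 = −0.05; SE = √(1/94.5 + 1/84) = 0.150; bias/SE = −0.333; type I error = 0.063.

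| p_C | p_A | D | Bias (SD) | Share of 0.41 | Type I error |
|---|---|---|---|---|---|
| 10% | 10% | 0.5 or 1 | 0 | 0 | 0.050 |
| 10% | 20% | 0.5 | −0.05 | 12% | 0.063 |
| 10% | 30% | 0.5 | −0.10 | 24% | 0.099 |
| 10% | 20% | 1 | −0.10 | 24% | 0.102 |
| 10% | 30% | 1 | −0.20 | 49% | 0.251 |

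The D = 1 rows show sensitivity to an extreme assumption. The first row is the important control: the same rate and the same kind of patient removed from each arm produces no bias. If more patients were removed from control, the sign would reverse.

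**The case against.** The strongest reply is that the article never says excluded patients leave the analysis. The list could be read as rules for ending participation, with the intention-to-treat sentence fixing the analysis set. The first item may only restate the right to withdraw that the Participants section guarantees. A condensed article also commonly leaves the handling of withdrawals to a fuller document. This stands in part: removal is an inference from the label given to the list, so the accurate claim is a conflict as written. It does not dispose of the point, because the article itself states both rules and they cannot both be followed literally.

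A reader might go further and infer that the criteria bite only in the app arm. The text does not support that. The first item concerns continuing with the research; unwillingness to keep using the app appears only as a limitation. Transfer and deterioration are worded for all patients. The inclusion criteria require smartphone use of everyone, and the Data Collection Instruments section collects questionnaire data online for the whole study, so phone access is not relevant to one arm only.

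A reader might also infer that clinicians who know the allocation decide who has deteriorated. The article says that the outcome assessor is unblinded, but not who makes that judgement.

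Finally, one could assume 15% lost from the app arm, none from control, and lost patients 0.5–0.8 SD worse than average. That gives 0.15 × 0.5 / 0.85 = 0.088 to 0.15 × 0.8 / 0.85 = 0.141 SD. But criteria worded for both arms do not produce losses in one arm alone. The outcome is also a change from baseline, so patients who are merely more distressed throughout need not differ on it.

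**Conclusion.** The conflict between the Exclusion Criteria and Statistical Analysis sections is real and rests on the article's own wording and timing. Followed literally, the list takes out randomised patients because of their later course, including those most likely to have the secondary outcomes.

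That the primary comparison will be biased, or biased towards the app, is not established. It requires removal that differs by arm in rate or in type of patient. This is plausible in an open trial with an unblinded assessor whose authors expect some patients to stop using the app, but nothing in the text prescribes it. Under the assumptions in the working (10% removed from control, 20–30% from the app arm, D = 0.5 on the change score), the distortion is 0.05–0.10 SD and type I error is about 0.06–0.10. These figures illustrate scale and are not forecasts.

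The power loss, 0.80 to about 0.75, applies only if total loss reaches 20% in both arms. The 10% allowance may or may not already cover these exclusions.

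**What to change.** Reconcile the two sections:

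1. State that the three items are eligibility checks applied only before the envelope is opened, worded as states at that moment.
2. Record any later occurrence as a post-randomisation event, not as an exclusion from the trial. Whether a patient goes on using the app is a clinical matter on which this point takes no position.
3. Continue DASS-21 at discharge and two weeks later in both arms wherever consent and the patient's condition allow.
4. Analyse every randomised patient in the assigned group, and report the number of losses and their reasons by arm.
5. Say whether the 10% attrition covers these events.

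The cost is one reworded section, some additional follow-up with a 21-item questionnaire, and handling of missing data, since some patients will withdraw consent or be too ill to answer. The estimate may come out less favourable to the app. The planned 105 per group does not change.
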